## Abstract

**Background and aims:**

Despite a steady decline in smoking rates across the United Kingdom (UK) over the past decades, substantial tobacco‐related inequalities persist, particularly among individuals with mental illness. Smoking prevalence in this group has remained largely unchanged, highlighting a major public health concern. This protocol outlines a trial aimed at addressing this issue by evaluating the effectiveness of offering an electronic cigarette (e‐cigarette) starter kit for smoking cessation and harm reduction as an adjunct to usual care to adults who smoke with mental illness treated in the community.

**Design:**

Two‐arm parallel randomized controlled superiority trial.

**Setting:**

A minimum of eleven UK National Health Service mental health Trusts or general practices.

**Participants:**

Adults who smoke with a diagnosis of mental illness treated in the community.

**Intervention and comparator:**

Participants will be randomly allocated (1 : 1) to receive: (i) an e‐cigarette starter kit, a brief demonstration and both verbal and written information on e‐cigarette use as an adjunct to usual care; or (ii) usual care alone.

**Measurements:**

The primary outcome is 7‐day point prevalence carbon monoxide‐validated abstinence, assessed six months after study enrolment or target quit date. Secondary outcomes include: 6‐month continuous abstinence defined by Russell Standard, self‐reported smoking abstinence at 1 month, ≥50% smoking reduction (cigarettes/day) at 1 and 6 months, mental health symptoms and general mood and physical symptoms at 1 and 6 months, cost‐effectiveness of the intervention and adherence to and satisfaction with the intervention.

**Comments:**

This will be the first large‐scale study in the UK to assess the effectiveness and cost‐effectiveness of providing an e‐cigarette starter kit for smoking cessation and harm reduction in people with mental illness. Results will inform policy and practice related to supporting smoking cessation for this population.

## INTRODUCTION

Tobacco smoking accounted for 15% of deaths in the UK general population in 2019 [1]. Tobacco‐related deaths and diseases are not evenly distributed across the population, with higher rates of tobacco‐related morbidities among individuals with mental health illness [2]. People with mental health illness are more than twice as likely to smoke compared with the general population, and there has been limited change in smoking prevalence among this group over the past five decades [2, 3, 4]. Despite being similarly motivated [5] and able to [6] quit smoking as those without mental illness, they face greater challenges owing to high nicotine dependence and limited access to support, including a reduced likelihood of prescribers offering stop‐smoking medication and a reduced likelihood of clinicians offering to refer them to stop‐smoking services [7]. Therefore, it is crucial to develop more effective and tailored smoking cessation strategies for this population.

Electronic cigarettes (e‐cigarettes), which provide nicotine without many of the harmful substances found in tobacco smoke, are increasingly recognized as a valuable tool for smoking cessation for people with mental illness [8]. In England, there has been an increase in their use as a smoking cessation tool [9, 10], with nicotine‐containing e‐cigarettes being included as a treatment component in national guidelines on the treatment of tobacco dependence [11]. In the general population, accumulating evidence indicates that nicotine e‐cigarettes are more effective than nicotine replacement therapy (NRT) in aiding smoking cessation [12, 13, 14]. Additionally, research conducted in Italy [15, 16], the USA [17], Australia [18] and the UK [19] suggests that e‐cigarettes can be effective for smoking cessation and reduction among adults with mental illness who smoke. While cessation remains the ideal outcome, smoking reduction also highlights the potential to reduce morbidity and mortality associated with smoking, as even partial reductions in cigarette consumption can yield health benefits [20]. Importantly, these studies did not find any evidence that e‐cigarettes adversely affect mental health, further emphasising their potential as a safe smoking cessation aid for individuals with mental illness. In fact, the uptake of e‐cigarettes appears particularly high among people with mental illness, who have been shown to be more likely to have tried and to currently use e‐cigarettes than the general population [21]. Several factors may contribute to this. First, e‐cigarettes are relatively inexpensive compared with both cigarettes and other cessation treatments [22]. Second, they offer a straightforward stand‐alone treatment that is easy to use. Third, unlike most NRTs, e‐cigarettes mimic the sensory experience of smoking and allow users to control their nicotine intake, which may appeal to people who are more dependent upon smoking and have previously struggled to quit [23]. As such, e‐cigarettes could be an important aid in efforts to address tobacco‐related health inequalities in this population, which has been identified as a health priority in England [24, 25]. As service models to improve the provision of tobacco dependence treatment are being rolled out across the country [25], it is important to advance the evidence base on the role that e‐cigarettes can play in these efforts.

To explore the feasibility and acceptability of supplying e‐cigarette starter kits, along with brief verbal and written advice on e‐cigarette use, as an adjunct to usual care for smoking cessation in adults who smoke with mental illness treated in the community, we conducted a feasibility study [26]. The results demonstrated that the trial and intervention were acceptable to both participants and health professionals delivering the treatment [26]. Although the target size was not achieved, the feasibility study obtained good consenting and adherence rates with limited contamination. Additionally, an exploratory analysis suggested trends favouring the intervention for continuous abstinence [for weeks 2–4 from the enrolment date or the target quit date (for those who set a date within 1 week of enrolment)], point prevalence abstinence (24‐hour abstinence) and ≥50% reductions in cigarette consumption [26, 27, 28]. The cost of the intervention was comparable with similar smoking cessation treatments for this population. Our feasibility study also demonstrated the feasibility of collecting data on healthcare resource use and quality of life among people with mental illness [26], which is essential for conducting a comprehensive health economic evaluation.

We used learning from the feasibility study to optimize the methodology for conducting a subsequent definitive RCT to evaluate the effectiveness and cost‐effectiveness of offering an e‐cigarette starter kit as an adjunct to usual care for smoking cessation and reduction in people with mental illness (ESCAPE), the protocol for which is presented here.

### Objectives

#### Primary

To assess the impact of offering an e‐cigarette starter kit intervention, compared with usual care alone, on 7‐day point prevalence carbon monoxide (CO)‐validated abstinence from smoking at the 6‐month follow‐up.

#### Secondary

To evaluate the impact of offering an e‐cigarette starter kit intervention, compared with usual care alone, on:
self‐reported continuous smoking abstinence at the 6‐month follow‐up;self‐reported smoking cessation rates at the 1‐month follow‐up;self‐reported smoking reduction at both the 1‐ and 6‐month follow‐ups;mental health outcomes and psychosocial measures at the 6‐month follow‐up.
To assess the cost‐effectiveness of offering the e‐cigarette starter kit intervention over and above usual care.To assess the adherence to and satisfaction with the e‐cigarette starter kit intervention.

## METHODS

### Design and setting

This is a two‐arm parallel randomized controlled superiority trial to assess the effectiveness of offering an e‐cigarette starter kit intervention, compared with usual care, for increasing abstinence rates at the 6‐month follow‐up (Data S1). The study will take place in a minimum of 11 primary and secondary care UK National Health Service (NHS) mental health trusts and general practices (GPs). Although specialist mental health services in England are mostly provided by mental health trusts, classified as secondary care, most patients with mental illness, particularly with common conditions such as anxiety and depression, are managed in primary care. Clinical contact with patients with mental illness in primary care is likely to be in the form of medication/mental health reviews, physical health checks or access to low‐intensity therapies. Patients managed in secondary care services are more likely to have severe, complex and enduring mental illness, such as schizophrenia and bipolar disorder, and receive treatment and care from specialist mental health professionals in multidisciplinary teams.

### Participants

Participants will be adults who smoke, have a diagnosis of mental illness based on their medical records, and meet all of the inclusion criteria and none of the exclusion criteria.

### Inclusion criteria

Participants will be included if they: (i) are aged ≥18 years; (ii) are self‐reported current cigarette smokers (in the past 7 days); (iii) have a diagnosis of mental illness (in accordance with UK NHS categorization, https://www.nhs.uk/mental-health/conditions/) and are currently being managed or receiving treatment for this in primary or secondary care, validated by their healthcare records; (iv) have the capacity to provide consent; and (v) are seriously considering quitting, cutting down or maintaining abstinence from tobacco.

### Exclusion criteria

Participants will be excluded if they: (i) have had a mental health inpatient admission in the last 3 months; (ii) have self‐reported current regular use of e‐cigarettes (at least weekly); (iii) have self‐reported current participation in another smoking cessation trial; (iv) are receiving current treatment for comorbid drug or alcohol problems to reduce the possibility of hospital admission for acute events (and thus the risk of dropout); (v) have a diagnosis of Alzheimer's disease or dementia; (vi) have a nut, citrus, nicotine or propylene glycol allergy; or (vii) are pregnant or breastfeeding.

### Treatment groups

#### Control

Participants in the control group will receive usual care related to smoking cessation in accordance with UK National Institute for Health and Care Excellence (NICE) guidelines. Usual care, which is free to access in the UK, varies between trusts and GP practices but is guided by NICE guideline NG209 [11]. At a minimum, it should include evidence‐based and very brief advice to stop smoking, which consists of the three As (Ask and record smoking status; Advice on the best way of quitting; and Act on patient response to build confidence) [29, 30], and a referral to in‐house or external specialist stop‐smoking services. Participants, regardless of their motivation to stop smoking, will be encouraged to consider quitting and to set a target quit date within a week of randomization. Those who do not wish to set a target quit date will be encouraged to reduce their cigarette consumption.

#### Intervention

Participants allocated to the intervention group will be offered an e‐cigarette starter kit, and a verbal explanation and demonstration, along with an information leaflet on how to use the e‐cigarette as an adjunct to the usual care outlined above. The e‐cigarette starter kit will contain a pod‐based e‐cigarette (ICON Vape), which is suction‐automated and uses pre‐filled 1.6‐mL pods containing 20 mg/mL nicotine e‐liquid. We chose a high nicotine concentration based on pervious work in this population, because smokers with mental illness have higher dependence [31] and e‐cigarettes with higher nicotine concentrations tend to be more effective [16]. All intervention participants will be provided with a 4‐week supply of refill pods (seven boxes) in tobacco, menthol and fruit flavours in a 1 : 2 : 2 ratio, based on the choice of flavour preferences observed during the feasibility study. All intervention participants will be able to choose the flavour of the final two boxes. The ICON Vape device was selected based on consumer research undertaken by the University of East Anglia [32, 33, 34], where it received high ratings for ease of use, satisfaction, taste and flavour options. All intervention participants, regardless of their motivation to stop smoking, will be encouraged to consider quitting and to set a target quit date within a week of randomization. They will be asked to start using the e‐cigarette as soon as possible and to seek out local or online vape shops to obtain further e‐liquid pods, suited to their individual needs and flavour preference. Participants who do not wish to set a target quit date will be encouraged to use the e‐cigarette to reduce cigarette consumption as soon as possible.

### Sample size

We aim to recruit 616 participants, with 308 participants asigned to each group. Pooling the results of the only three RCTs comparing e‐cigarettes with placebo e‐cigarettes [15, 35, 36] yielded an expected effect size of risk ratio (RR) = 2.01 for 6‐month abstinence rates. We consider this estimate to be conservative as most of these trials used older, less effective first‐generation e‐cigarettes. In fact, recently published trials comparing active treatment (NRT) with a modern third‐generation e‐cigarette in the context of stop‐smoking services [12] found a superior effect of e‐cigarettes on 6‐month abstinence rates of RR = 1.63. Based on established effect estimates for NRT versus placebo from high‐quality trials [37], findings from this trial therefore indirectly suggest that, compared with placebo/usual care, third‐generation e‐cigarettes (as will be used in this trial) may increase 6‐month abstinence rates by nearly threefold (RR = 2.62). Given the low abstinence rates in the control conditions observed in the feasibility study [26], we revised the expected abstinence rates in the control (standard care) group from 7.7% (based on previous trials with people with mental illness) [38, 39] to 5.0%. Based on the feasibility study results (finding an absolute risk difference of 9.5%) [26] and the fact that a modern e‐cigarette is used, we assume an effect estimate of RR = 2.62, as found in more recent trials, to be most appropriate. We therefore expect an absolute predicted risk difference of 8.1%, assuming 6‐month abstinence rates of 5% in the control group and 13.1% in the intervention (e‐cigarette) group. A sample of 616 participants (308 per group) would provide more than 90% power to detect this effect, with an alpha level of 0.05 in two‐tailed analysis. This sample size would also provide 80% power to detect a more conservative effect of RR = 2.32 (intermediary between effect estimates from older and effect estimates from more recent trials using modern e‐cigarettes), with an absolute predicted risk difference of 6.6% at the 6‐month follow‐up (5.0% for the control group vs 11.6% for the treatment group).

No adjustment for attrition is applied to the sample size calculations, as participants lost to follow‐up will be classified as people who smoke, as defined by the Russell Standard [40]. There is also no inflation using a design effect to account for clustering in trusts as it is assumed that the intra‐cluster correlation is likely to be very small or negligible [41].

### Procedure

Figure 1 presents the study flow diagram and Table 1 presents the schedule of assessment at baseline and at the follow‐ups.

**FIGURE 1 add70115-fig-0001:**
[figure not shown]
Study flow chart.

**TABLE 1 add70115-tbl-0001:** Schedule of enrolment, interventions and assessments.

Activities	Study period			
	Identification	Allocation	Follow‐up	
	Baseline	0	1 month	6 months
**Enrolment**				
Eligibility screen	x			
Informed consent	x			
Allocation		x		
**Interventions**				
Usual care		x		
E‐cigarette starter kit, brief demonstration, verbal and written information on e‐cigarette use as an adjunct to usual care		x		
**Assessments**				
Socio‐demographic characteristics	x			
Nicotine dependence	x			
Motivation to quit	x			
Age started smoking	x			
Smoking duration	x			
Past year quit attempts	x			
Current use of tobacco products other than cigarettes	x			
Ever e‐cigarette use as smoking cessation aid	x			
AUDIT‐C	x			x
Physical activity	x			x
Fruit and vegetable consumption	x			x
Patient Heath Questionnaire‐9	x		x	x
Generalized Anxiety Disorder Scale‐7	x		x	x
7‐day point prevalence			x	x
Sustained abstinence				x
50% smoking reduction			x	x
CO breath sample				x
General mood and physical symptoms			x	x
Adverse events			x	x
Use of e‐cigarette			x	x
Healthcare service use	x		x	x
Health‐related quality of life	x			x

Socio‐demographic characteristics include age, sex, employment status, ethnicity, education, accommodation type and marital status.

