##### Secondary outcomes measures

Continuous abstinence at the 6‐month follow‐up, defined as not having had more than five cigarettes in the period from 2 weeks after baseline to the follow‐up, in line with the Russell Standard [40]. Self‐reported smoking abstinence at 2–4 weeks from baseline or target quit date (whichever is later). Fifty percent smoking reduction at 1‐ and 6‐month follow‐ups, calculated by the reduction in self‐reported cigarettes per day from baseline. Number of unsuccessful quit attempts at the 1‐ and 6‐month follow‐ups.

Mental health symptoms assessed by Patient Health Questionnaire‐9 (PHQ‐9) [43] and General Anxiety Disorder‐7 (GAD‐7) [44], general mood, physical symptoms assessed by the Mood and Physical Symptoms Scale (MPPS) [45, 46], and experience of adverse events at the 1‐ and 6‐month follow‐ups, similar to previous research [23].

Cost‐effectiveness of the intervention based on health economics measures outlined below.

The fidelity of intervention implementation and satisfaction with the intervention at the 1‐ and 6‐month follow‐ups will be based on questions related to e‐cigarette use in the past month as well as a question to assess whether the e‐cigarette used in the last month was the device provided to intervention participants as part of the study.

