#### Baseline measures

We will record age, sex, employment status, ethnicity, education, accommodation type and marital status (Table 2), as well as most recent diagnosis and acute events (e.g. hospitalization) in the last year based on the participants' medical records. We will also assess nicotine dependence with the Strength of Urges to Smoke Scale [47] and motivation to quit with the Motivation to Stop Scale [48]. Age started smoking, smoking duration, past year quit attempts, current use of tobacco products other than cigarettes and ever e‐cigarette use as a smoking cessation aid will also be recorded. Alcohol use will be measured using the Alcohol use disorders identification test for consumption (AUDIT‐C) [49]. Physical activity (strength training; moderate or vigorous aerobic physical activity) will be assessed with questions from the Allied Dunbar National Fitness survey [50]. Consumption of at least five portions of fruit and vegetables (Healthy Eating Index) [51] will also be recorded.

**TABLE 2 add70115-tbl-0002:** Measures of participant sociodemographic characteristics.

Characteristic	Question	Answer options
Age	What is your age?	18–99 years
Gender	What is your gender?	(i) Male (ii) Female (iii) Other
Ethnicity	How would you describe your ethnic background?	(i) White (ii) Mixed/Multiple (iii) Asian/Asian British (iv) Black/African/Caribbean/Black (v) British (vi) Chinese (vii) Arab (viii) Other
Education	What is your highest educational qualification?	(i) GCSE/O‐level/CSE (ii) Vocational qualification (iii) A‐level or equivalent (iv) Bachelor’s degree or equivalent (v) Master’s/PhD or equivalent (vi) No formal qualifications (vii) Other
Employment status	How would you describe your employment status?	(i) Employed full‐time (ii) Employed part‐time (iii) Self‐employed (iv) Retired (v) Student (vi) Voluntary worker (vii) Not employed but seeking work (viii) Not employed but not seeking work because of ill health (ix) Not employed but not seeking work for other reason (x) Other
Accommodation type	What is your current accommodation type?	(i) Purchasing with a mortgage (ii) Owned outright (iii) Rented from the local authority (iv) Rented from a private landlord (v) Rented from a housing association/trust (vi) Other
Marital status	What is your marital status?	(i) Single (ii) Married (iii) Living with partner/cohabiting (iv) Divorced/separated (v) Widowed (vi) Other

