#### Primary analysis

The effect of treatment on the primary outcome (CO‐verified 7‐day abstinence rates at the 6‐month follow‐up) will be analysed by a mixed‐effect (multilevel) logistic regression model with fixed treatment and a random intercept for site, included to allow for any site‐level variation in treatment effect. We will employ a likelihood ratio (LR) test to assess the significance of including the random site effects by comparing the mixed‐effects model with a model including only fixed effects. In addition, we will calculate the intraclass correlation coefficient (ICC) to quantify the proportion of variance in the primary outcome attributable to differences among clinical sites.

Secondary outcomes at the 1‐ and 6‐month follow‐ups will also be analysed as described above if they are binary, or with mixed effects (multilevel) linear regression adjusting for site‐level variation if they are continuous numeric variables. Mean difference will be reported. For regressions, we will check the assumptions of normality of the residuals.

We will use a repeated measures analyses to examine changes in cigarette consumption (a reduction of ≥50%) and mental health symptoms across baseline, and the 1‐and 6‐month follow‐ups. For continuous mental health symptom scores, we will use a multilevel linear regression model. We will verify the assumptions of normality and homoscedasticity of the residuals using quantile–quantile (QQ) plots and residual versus fitted plots. If these assumptions are not met, we will apply appropriate transformations (e.g. log transformation for positively skewed data). For the binary outcome of a ≥50% reduction in cigarette consumption, we will use a mixed‐effects logistic regression model. We will assess for overdispersion by comparing the residual deviance with the degrees of freedom and will consider alternative models, such as negative binomial regression, if overdispersion is present. Our models will incorporate fixed effects for the intervention group, time (treated as a categorical factor) and their interaction to assess differential changes between groups over time. To account for individual variability, we will include random intercepts for each participant and clinic site.

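### The mood and physical symptoms scale has no baseline measurement, so this secondary outcome loses precision and its change from before quitting cannot be described

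*Protocol article*

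**What the plan says.** The Assessments block of Table 1 has a row "General mood and physical symptoms" with marks under 1 month and 6 months, and blanks under baseline and time 0. In the same block, the PHQ-9 row ("Patient Heath Questionnaire", as printed) and the GAD-7 row are marked at baseline, 1 month and 6 months. AUDIT-C and health-related quality of life also have a baseline mark.

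The section on secondary outcome measures names the instrument ("physical symptoms assessed by the Mood and Physical Symptoms Scale") and places it at 1 and 6 months. No other section schedules it earlier.

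Under Primary analysis, continuous secondary outcomes are to be compared by mixed linear regression "adjusting for site‐level variation if they are continuous numeric variables". No baseline covariate is named. A separate repeated-measures analysis covers cigarette consumption and "mental health symptoms across baseline, and the 1‐and 6‐month follow‐ups".

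**The concern.** Participants are under treatment for mental illness, so some will have low mood and other symptoms at entry. A follow-up score on this scale mixes those symptoms with any effect of quitting or of the e-cigarette. With no pre-treatment score, two things are lost. The report cannot say whether symptoms rose or fell from before quitting in either arm, and the between-arm comparison cannot use the scale's own baseline to remove stable differences between people.

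The scale is one of the outcomes closest to short-term tolerability. Adverse events, the other direct symptom measure, also have no baseline mark. Less precision means that a modest worsening in one arm is easier to miss.

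**Working it through.** **Schedule check, from Table 1**

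| Measure | Baseline | 1 month | 6 months |
|---|---|---|---|
| PHQ-9 | x | x | x |
| GAD-7 | x | x | x |
| Mood and physical symptoms | – | x | x |

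The evidence is the blank cell in an existing row. The Baseline measures section does not name the scale, but it does not name PHQ-9 or GAD-7 either, so its silence proves nothing.

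**The plan's own figures.** The article gives no power or precision figure for this scale. Its stated power concerns the primary binary outcome. With 308 per group and two-sided alpha 0.05, power for 5% versus 13.1% comes to 94.1%, in line with the stated figure of more than 90%. For 5.0% versus 11.6%, 80% power needs 303 per group with a continuity correction, close to 308. The present point does not affect these figures.

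**Precision for the scale.** Inputs: 308 per group and two-sided alpha 0.05 (Sample size section), complete follow-up (assumed), and a baseline-to-follow-up correlation r (assumed, since none is given).

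- Variance with own-baseline adjustment relative to none: 1 − r².
- Equivalent sample size ratio: 1/(1 − r²).
- Detectable difference at 80% power, in SD units: (1.960 + 0.842) × √(2/308) × √(1 − r²) = 0.226 × √(1 − r²).
- Power at a true difference of 0.2 SD: Φ(0.2 / [0.0806 × √(1 − r²)] − 1.960), where 0.0806 = √(2/308).

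| r | 1 − r² | Variance cut | Equivalent extra participants | Detectable difference (SD) | Power at 0.2 SD |
|---|---|---|---|---|---|
| no baseline | 1.00 | – | – | 0.226 | 69.9% |
| 0.4 | 0.84 | 16% | 19% | 0.207 | 77.3% |
| 0.5 | 0.75 | 25% | 33% | 0.196 | 81.8% |
| 0.6 | 0.64 | 36% | 56% | 0.181 | 87.3% |

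Counting losses to follow-up as smoking does not supply a missing symptom score, so real precision would be lower. With 246 per group (about 80% follow-up, assumed), the detectable difference is 0.253 SD without a baseline and 0.219 SD at r = 0.5.

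**What PHQ-9 and GAD-7 could recover.** The figures above compare own-baseline adjustment with the site-only model. Suppose the baseline PHQ-9 and GAD-7 scores together correlate 0.4 with the follow-up score and add nothing once the own baseline (r = 0.5) is known. The further gain from the own baseline is then 1 − 0.75/0.84 = 11%, not 25%. The documents do not give the real figure.

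**Chance imbalance.** With 308 per group, the standard error of a baseline difference between arms is √(2/308) = 0.08 SD. At r = 0.5, a difference of that size moves the follow-up contrast by 0.5 × 0.08 = 0.04 SD.

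**The case against.** The strongest reply is that nothing planned is broken. The trial sets this scale at 1 and 6 months, alongside adverse events, and compares the arms at those times. Randomization makes that comparison valid, and the confidence interval already allows for chance imbalance. Symptom change is covered by PHQ-9 and GAD-7 at three time points, and these scores could also serve as covariates here. The site-only model uses no baseline covariate, so adding the item gains no precision unless the model changes too. Recruitment was planned from March 2024 to the end of 2024, so the item may come too late for many participants.

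Most of this stands. It keeps the point small and makes the quoted gains upper bounds. It does not remove the point: PHQ-9 and GAD-7 measure depression and anxiety and are only partial substitutes, and the scale's own starting level remains unknown.

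A reader might infer more than the documents support:

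- *That the repeated-measures analysis cannot be run.* The section on secondary outcome measures ties mental health symptoms to PHQ-9 and GAD-7 and lists general mood and physical symptoms apart from them. Both questionnaires have a baseline, so the planned analysis fits Table 1.
- *That pre-existing symptoms make up most of the spread in follow-up scores.* The documents give no such figure. It would need r² above 0.5, that is r above about 0.71, which is higher than the range assumed here.
- *That the outcome cannot be adjusted at all.* Only adjustment for its own baseline is impossible.

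**Conclusion.** The point holds as a minor design improvement. The schedule explicitly omits a baseline for one secondary outcome, while the companion mental health scales have one. The consequences are no description of change from before quitting and a loss of precision. Relative to the site-only model, own-baseline adjustment would cut variance by 16% to 36% if r lies between 0.4 and 0.6. Relative to a model with baseline PHQ-9 and GAD-7, the cut would be smaller by an unknown amount. The range of r is an assumption, and the power figures also assume complete follow-up. The between-arm comparison is not biased, and the primary outcome is untouched.

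**What to change.** - **If enrolment is open:** mark the scale at baseline in Table 1, add it to the in-person questionnaire completed before randomization, and adjust the 1- and 6-month scores for it. State in advance how the missing baseline of earlier participants is handled. A missing-value indicator would serve, because whether the item was asked is settled before randomization.
- **For participants already enrolled, or if enrolment has closed:** adjust for the baseline PHQ-9 and GAD-7 already collected, and state that only between-arm differences at follow-up will be reported for this scale.
- **If the full protocol does collect the scale at baseline:** correct Table 1.

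The cost is about a minute per participant, a minor amendment, and a covariate that earlier participants lack. Using PHQ-9 and GAD-7 as covariates needs no new data, only a line in the analysis plan.
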